### Study endpoints

The primary endpoint is the number of ventilator-free days and alive at day 28, defined as the number of days from day 1 to day 28 the patient is alive and breathes without invasive assistance of the mechanical ventilator for at least 24 consecutive hours. To calculate this endpoint all relevant data will be taken into account and collected, including repeated re-intubation and -extubation.

Secondary endpoints are subdivided into clinical outcome variables and health-economic outcome variables. Clinical outcome variables include: ICU- and hospital length of stay (LOS), ICU-, hospital-, and 90-day mortality, development of ARDS, VAP, development of atelectasis and presence of pneumothorax and cumulative use and duration of use of sedatives, cumulative use and duration of use of neuromuscular blocking agents (other than used for intubation), and ICU-acquired weakness and delirium. Health-economic variables include incremental cost per ICU-day avoided and incremental cost per mechanical ventilation-day avoided.

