### Follow-up

On ICU admission and within the first 24 hours, demographic and baseline data, as well as data on disease severity are collected. Data collection includes: gender, age, height, weight, reason for ICU admission, reason for ventilation, cause of respiratory failure, the Acute Physiology and Chronic Health Evaluation II (APACHE II) score and the Simplified Acute Physiology Score II (SAPS II).

Data on standard of care and clinical outcome variables (described below) are collected on a daily basis every day until day 28, discharge of the ICU or death, whichever comes first. Data on duration of ventilation, length of stay in ICU and hospital, location of the patient (in ICU, hospital, other facility, or home) and life status (alive or deceased) are assessed on days 28 and 90.

The following variables are collected daily: respiratory status; intubation status (if extubated: time of extubation/if re-intubated: time of re-intubations) tracheostomy status (if tracheostomized: time of tracheotomy), invasiveness of ventilation (invasive, non-invasive, or intermittent ventilation via tracheostomy), need for decreasing instrumental dead space; development of pulmonary complications (moderate or severe ARDS, pneumonia, atelectasis and pneumothorax); cumulative use and duration of sedatives and neuromuscular blocking agents; sedation score using the RASS [27, 28]; level of pain (NRS or VAS or CCPOT or BPS); delirium score with the Confusion Assessment Method for ICU (CAM-ICU) score [30, 31]; presence of ICU-acquired weakness using Medical Research Council (MRC) score [32] or Grip Strength Assessment [33].

The following mechanical ventilation parameters are collected within 1 hour before and 1 hour after randomization, and every day at a fixed time point until cessation of ventilation: tidal volume in ml and ml/kg PBW, respiratory rate, level of PEEP, peak and plateau pressures, or level of pressure support and maximal airway pressure, inspiration to expiration ratio, inspired oxygen fraction, minute volume, pulmonary compliance, Lung Injury Score (LIS: based on chest X-ray findings, PaO_2_/FiO_2_, PEEP level and respiratory compliance) [34] and Oxygenation Index [35].

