ICU-related therapy variables to collect daily include: respiratory parameters and arterial blood gas analysis (once daily), amount and type of infused products including blood products and fluids (crystalloids and (artificial) colloids), cumulative fluid balance and Sequential Organ Failure Assessment (SOFA) score [36].

Resource use parameters and unit prices are collected to estimate health care costs from a health systems perspective and include costs of ventilation, costs of stay in ICU, costs of stay in hospital, costs of cumulative use of sedatives, costs of neuromuscular blocking agents, costs of use of tracheostomies and costs of ventilator-associated pneumonia (VAP).

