### Statistical analysis

The primary outcome, the number of days alive and free of ventilation at day 28, will be analyzed using Cox’s regression. Possible imbalance between groups will be modeled in the Cox model. *P*-values of 0.05 are used for statistical significance. When appropriate, statistical uncertainty will be expressed by the 95 % confidence levels. All statistical analyses will be performed with the R language and environment for statistical computing.

Continuous normally distributed variables will be expressed by their mean and standard deviation or when not normally distributed as medians and their interquartile ranges. Categorical variables will be expressed as n (%). To test groups Student’s *t*-test will be used, if continuous data is not normally distributed the Mann-Whitney *U*-test will be used. Categorical variables will be compared with the Chi-square test or Fisher’s exact tests. Time dependent data will be analyzed using a proportional hazard model adjusted for possible imbalances of patients’ baseline characteristics. Analysis will be performed with R statistics version 3.0.2 (R Foundation, Vienna, Austria). Patient characteristics will be compared and described by appropriate statistics.

The goal of the primary analysis is to quantify the effect of ventilation using low tidal volumes versus ventilation using high tidal volumes on the number of ventilator-free days and alive at day 28. Statistical analysis will be based on the intention-to-treat principle. We will also perform a per-protocol analysis, comparing patients who received lower tidal volumes and patients who received higher tidal volumes. Other secondary analyses include*:* patients who had pneumonia versus patients without pneumonia, and patients with sepsis versus patients without sepsis.

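### The economic endpoints count ICU-days and ventilation-days avoided with no survival term, so an arm with more early deaths can look both cheaper and more effective

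*Protocol article*

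**What the plan says.** All references are to the Methods of the protocol article.

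- **Study endpoints, economic.** "Health-economic variables include incremental cost per ICU-day avoided and incremental cost per mechanical ventilation-day avoided".
- **Study endpoints, primary.** A day from 1 to 28 counts only if "the patient is alive and breathes without invasive assistance of the mechanical ventilator for at least 24 consecutive hours". Days after death therefore earn nothing.
- **Study endpoints, clinical secondary.** "Clinical outcome variables include: ICU- and hospital length of stay (LOS), ICU-, hospital-, and 90-day mortality", followed by the complications. No rule for deaths is given for length of stay.
- **Follow-up, costs.** The cost components "include costs of ventilation, costs of stay in ICU, costs of stay in hospital", then sedatives, neuromuscular blockers, tracheostomies and ventilator-associated pneumonia.
- **Follow-up, data.** Daily collection runs "every day until day 28, discharge of the ICU or death, whichever comes first". Duration of ventilation, ICU and hospital stay, location and "life status (alive or deceased) are assessed on days 28 and 90".
- **Statistical analysis.** Continuous data get a t-test or, "if continuous data is not normally distributed the Mann-Whitney" test. "Time dependent data will be analyzed using a proportional hazard model adjusted for possible imbalances" in baseline characteristics. Length of stay is not assigned to either method.

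**The concern.** A patient who dies on day 2 uses two ICU-days at most. When the unit of effect is a day avoided, that death counts as a gain over a survivor who needed ten days. The main cost items are priced by the same days, so the death also lowers the cost. Numerator and denominator then both move in favour of the arm with more deaths.

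The error works in the other direction too. A strategy that saves lives can appear to add ICU-days and cost. The primary endpoint was built to avoid this, and the economic endpoints drop that protection. Within one trial, the primary result and the cost ratios could point in opposite directions.

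**Working it through.** **The plan's own figure.** The article gives no figure for length of stay or for the cost ratios. Its only related figure is the primary sample size: difference 1 day, SD 5, two-sided 0.05, power 80%. The normal formula gives 2 × (1.960 + 0.842)² × 5² / 1² = 392.4, so 393 per arm, and the t-test version gives 394. The article states 397, for which power is 80.5%. Then 397 × 1.2 = 476.4, matching 476 per arm. The figure reproduces, and this point does not touch it.

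**Days avoided.** Let p be mortality, S the mean ICU stay of survivors and D the mean ICU stay of those who die. Let S and D be the same in both arms, so the strategy does nothing for stay.

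Mean stay = (1 − p) × S + p × D

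Days avoided per patient by the arm with higher mortality = (p₁ − p₀) × (S − D)

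The article gives none of p, S or D, so all values here are assumptions. With S = 10 days, p₀ = 25% and p₁ = 30%:

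| D (days) | Mean stay, 25% arm | Mean stay, 30% arm | Days avoided per patient | Per 476 patients |
|---|---|---|---|---|
| 4 | 8.5 | 8.2 | 0.3 | 143 |
| 6 | 9.0 | 8.8 | 0.2 | 95 |
| 8 | 9.5 | 9.4 | 0.1 | 48 |
| 10 | 10.0 | 10.0 | 0 | 0 |
| 14 | 11.0 | 11.2 | −0.2 | −95 |

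Every row carries 476 × 0.05 = 23.8 extra deaths. At 25% v 35% the figures double: for D = 4, 0.10 × 6 = 0.6 day. With S = 14 and D = 5, at 25% v 30%, the result is 0.05 × 9 = 0.45 day.

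**Cost.** If an ICU-day costs c and nothing else differs, the first row gives an incremental cost of −0.3c with 0.3 day avoided. That reads as a strategy that saves money and is more effective, yet it consists only of extra deaths.

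**Ventilation-days.** The same formula applies with ventilation days in place of stay. The condition is that those who die have fewer ventilation days than survivors. This is harder to meet than the ICU condition, because survivors leave the ventilator before they leave the ICU.

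**Contrast with a unit that contains survival.** Assume survivors are ventilated for 6 days and those who die are credited with none. Survivors then have 28 − 6 = 22 ventilator-free days. The means are 0.75 × 22 = 16.5 and 0.70 × 22 = 15.4, a difference of −1.1. This unit moves against the arm with more deaths.

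**Length of stay, if all patients were tested as they are.** I simulated 3,000 trials of 476 per arm with gamma-distributed stays (shape 1.5), S = 10 and D = 4. The higher-mortality arm had the shorter mean stay in 73% of trials at 25% v 30%, and in 89% at 25% v 35%. The Mann-Whitney test was significant in its favour in 10% and 30%.

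**The case against.** The strongest reply is that nobody would read the ratios alone. ICU, hospital and 90-day mortality are listed as endpoints, the primary endpoint gives no credit after death, and a data and safety monitoring board follows safety. The economic variables come last in the list of endpoints and do not appear in the abstract. The list says that the variables include these two, so others may follow. All of this stands and limits the harm. It does not correct the ratios, whose unit is fixed in the text.

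The bias is also conditional. It needs a mortality difference and deaths that come early relative to survivors' discharge. The table shows it vanishing and then reversing. This stands too.

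A reader might infer that the plan counts deaths as short stays when it compares length of stay, or that it censors them in the hazard model. The article says neither. It assigns length of stay to no test and does not say whether death is an event, censored or competing. A condensed article commonly leaves that to the full protocol or analysis plan. The simulation shows only what would follow from an unadjusted comparison.

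A reader might also set the 0.1 to 0.3 day against the 1 day in the sample-size section. These are unlike quantities: the 1 day concerns ventilation and ventilator-free days, and no ICU-stay benefit is planned. Nor does the text support extending the point to ARDS or pneumonia, for which it assigns no time-to-event analysis.

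**Conclusion.** The point holds for the two economic endpoints. Their stated unit of effect has no survival term, and early death lowers both the days and the main costs. The spurious gain is 0.1 to 0.3 ICU-day per patient for 5 points of excess mortality, if survivors stay 10 days and those who die stay 8 down to 4. It is zero at equal stays and −0.2 day if those who die stay 14 days. These figures are illustrations, since the article supplies no mortality or stay data.

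The length-of-stay part is only a recommendation to state the rule for deaths. The bias is confined to secondary endpoints. It should be corrected, but it does not threaten the trial's main conclusion.

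**What to change.** 1. In Study endpoints, define the economic effect as incremental cost per ventilator-free day gained (the primary endpoint) and per ICU-free day alive gained, both to day 28.
2. Keep cost per ICU-day and per ventilation-day avoided as descriptive results only, shown beside mortality in each arm.
3. Where ICU and hospital stay are compared between arms, use ICU-free and hospital-free days, or time to discharge alive with death as a competing event. Do not use a plain t-test or Mann-Whitney test on all patients.

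The change is mainly wording and is best made before results by arm are seen. Ventilator-free days are already the primary endpoint, and ICU stay and life status are recorded at day 28. If days are to be counted up to a death after ICU discharge, or hospital stay is followed to day 90, check that the case report form holds the date of death: the article mentions only life status at days 28 and 90. The small loss is that the new ratios compare less directly with earlier figures for cost per day avoided, which the descriptive results partly preserve.

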### Statistical considerations

We will include a total of 952 patients. The required sample size is calculated using data from the recently published meta-analysis [11] and a secondary analysis of this meta-analysis using individual patient data from the studies performed in ICU patients [37]. The sample size is computed and based on the hypothesis that ventilation with low tidal volumes is associated with a reduction of 1 day of ventilation. A sample size of 397 patients in each group has 80 % statistical power to detect a difference of 1 ventilator-free day and alive at day 28 after ICU admission, assuming that the common standard deviation is 5 using a 2 -group *t-*test with a 0.05 2-sided significance level. The sample size is increased by 20 % to correct for dropouts and those lost to follow-up meaning that each group will contain 476 patients.

For this study we will include patients using a strategy using deferred informed consent because we explicitly want to randomize and start ventilation according to randomization within 1 hour after start of ventilation, or within 1 hour after admission if ventilation was initiated in the emergency room or the operation room. Nevertheless, written informed consent from the legal representative will be requested as soon as possible thereafter, and never later than 24 hours after randomization. If informed consent is not obtained within those 24 hours, or if a legal representative denies participation within this time frame, the patient is excluded and data will no longer be used, nor will this patient be counted for the sample size of 476 inclusions in each group (that is the provisionally included patient for whom informed consent is not obtained within the time frame of 24 hours is ‘replaced’ by a new patient, until the total number of 476 patients in each arm is definitively included).

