## Discussion

PReVENT is the first randomized controlled trial that is sufficiently powered to test the hypothesis that a ventilation strategy using low tidal volumes, as compared to a ventilation strategy using high tidal volumes, benefits patients without ARDS with regard to the clinically relevant endpoint of duration of ventilation.

It is increasingly becoming clear that ventilation *per se* has the potential to initiate lung injury or ARDS, mainly due to over-distension of (parts of) the lung [2]. Since a generally employable alternative treatment for ventilation is not yet at our disposal, the prevention of over-distension and lung injury should be the target. Earlier clinical studies indicated that ventilation using low tidal volumes could prevent development of lung injury by avoiding excessive stretch, and that high tidal volumes are more likely to cause damage in patients without ARDS [22]. A sufficiently-powered randomized controlled trial investigating the effects of low tidal volume ventilation in patients without ARDS is presently lacking. PReVENT follows an earlier randomized controlled trial in The Netherlands [21] that was prematurely stopped because of an unexpected benefit (that is reduction in development of new ARDS). In contrast to the previous randomized controlled trial, PReVENT uses duration of ventilation as primary endpoint. This endpoint is objective and foremost clinically relevant. Namely, protracted use of ventilation is associated with serious physiological and psychological sequelae. Complications associated with ventilation are well-known and include VAP and ICU-acquired weakness. Psychological sequelae associated with protracted use of ventilation are post-traumatic stress disorder [38–40], anxiety and depression [41], delirium [30, 42] and cognitive deficits [43]. Also, from an economic perspective, any intervention that shortens duration of ventilation and/or ICU length of stay is highly relevant.

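### SD 5 is not shown to belong to the 0–28 ventilator-free-day score; unless only a few percent of patients score zero, t-test power for 1 day is below the stated 80%

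*Protocol article*

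**What the plan says.** Under Statistical considerations, the Protocol article bases the sample size on the hypothesis that low tidal volume ventilation "is associated with a reduction of 1 day of ventilation". The next step changes the variable. With 397 patients per group, the stated power is 80% for a "difference of 1 ventilator-free day and alive at day 28 after ICU admission, assuming that the common standard deviation is 5". The test assumed for sizing is a two-group t-test at two-sided 0.05. Adding 20% for losses gives 476 per group, hence "We will include a total of 952 patients". The inputs are attributed to a meta-analysis and to an individual-patient-data analysis of its ICU studies. The article does not say which variable the SD of 5 describes.

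Under Study endpoints, the primary endpoint is "defined as the number of days from day 1 to day 28 the patient is alive and breathes without invasive assistance", with a condition of at least 24 consecutive hours. It is therefore a count from 0 to 28.

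Under Statistical analysis, the primary outcome is to be analysed by Cox regression.

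The Discussion opens with "PReVENT is the first randomized controlled trial that is sufficiently powered to test the hypothesis", its closing paragraph again calls the trial adequately powered, and the Discussion part of the Abstract says that enough patients are recruited to test the hypothesis. None of these three statements repeats the condition on the SD.

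**The concern.** Duration of ventilation and ventilator-free days are different variables with different variances. On the ventilator-free-day score, a patient who dies while ventilated, or who is ventilated throughout the 28 days, scores 0, whereas a patient weaned early scores in the twenties. A cluster at 0 far from the bulk of the scores inflates the SD quickly. The population is ICU patients expected to need more than 24 hours of ventilation, and ICU, hospital and 90-day mortality are all secondary endpoints, so some zeros must be expected.

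The SD of 5 alone turns a 1-day target into 397 per group. If the SD on the score is larger, the trial may miss a 1-day effect, and a reader who relies on the power claims could take a null result as ruling that effect out.

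**Working it through.** **Inputs from the Protocol article:** difference 1 day, SD 5, two-sided alpha 0.05, 397 per arm (476 after adding 20%), two-group t-test, score range 0–28.

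**Inputs not in the article, assumed here:** the share of patients scoring zero (p), and the mean (m) and SD (s) of the scores of all other patients.

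**1. The plan's own figure.** Power ≈ Φ(Δ / (SD·√(2/n)) − 1.96). With Δ = 1, SD = 5, n = 397: √(2/397) = 0.0710; 1/(5 × 0.0710) = 2.82; 2.82 − 1.96 = 0.86; power 80.4% by the exact t calculation. The n needed for 80% is 394, against 397 stated. 397 × 1.2 = 476.4, which matches 476. The arithmetic reproduces.

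**2. How many zeros an SD of 5 allows.** For a mixture of zeros and non-zero scores,

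SD² = (1 − p)s² + p(1 − p)m².

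With no spread among the others (s = 0), the SD is m√(p(1 − p)). Setting this to 5 gives the largest possible p:

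| Mean of the others, m | Largest p, s = 0 | Largest p, s = 3 | Largest p, s = 4 |
|---|---|---|---|
| 15 | 12.7% | 8.1% | 4.5% |
| 20 | 6.7% | 4.3% | 2.4% |
| 24 | 4.5% | 2.9% | 1.6% |

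If the others already have SD 5 around a mean of 20, even 2% zeros raises the overall SD to 5.7.

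**3. Power over an assumed range.** Take m = 20 and s = 5. For p = 5%: SD² = 0.95 × 25 + 0.05 × 0.95 × 400 = 23.75 + 19.0 = 42.75, so SD = 6.54. For p = 35%: SD² = 0.65 × 25 + 0.35 × 0.65 × 400 = 16.25 + 91.0 = 107.25, so SD = 10.36. The difference detectable with 80% power is SD·√(2/n)·(1.96 + 0.84).

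| Assumed zeros | Overall SD | Power for 1 day, 397 per arm | Power for 1 day, 476 per arm | Detectable difference, 397 per arm |
|---|---|---|---|---|
| 5% | 6.5 | 58% | 65% | 1.3 days |
| 10% | 7.6 | 45% | 52% | 1.5 days |
| 20% | 9.2 | 34% | 39% | 1.8 days |
| 35% | 10.4 | 27% | 32% | 2.1 days |

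**4. If the low scorers are not all exactly zero.** The endpoint definition lets a patient who dies after extubation keep some days. Suppose 10% or 30% of patients have scores spread uniformly over 0–10 days (mean 5, variance 100/12 = 8.33), and the rest have mean 20 and SD 5. For 10%: SD² = 0.1 × 8.33 + 0.9 × 25 + 0.1 × 0.9 × 15² = 0.83 + 22.5 + 20.25 = 43.58, SD 6.6, power 57% at 397 per arm. For 30%: SD² = 2.5 + 17.5 + 47.25 = 67.25, SD 8.2, power 40%. Partial credit softens the effect but does not bring the SD back to 5.

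**The case against.** A reader might go further and infer that a 0–28 score cannot have an SD of 5, that the trial therefore lacks its stated power, and that it could not detect a 1-day difference. The document does not support that reading, for these reasons:

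- An SD of 5 is possible with few zeros, as step 2 shows. The argument is one of implausibility, and it rests on a zero fraction that the article does not give.
- The endpoint definition does not set every death to zero, so the cluster at zero may be smaller than mortality.
- The 80% is stated conditionally on SD 5 and is correct on that condition.
- The planned primary analysis is Cox regression, whose power is not determined by the SD of the score. The figures above are power for the document's own sizing method and not for the primary test.
- The two cited analyses cannot be seen here. The move from duration to ventilator-free days suggests that the SD may describe duration, but does not prove it. A condensed article may also leave the derivation to the full protocol.

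All of this stands and limits the claim. It does not justify SD 5 for the score, and no other part of the article does so. The t-test is the only power calculation in the article, so the choice of Cox regression gives the 80% no separate support. The Discussion and Abstract also drop the condition on which the 80% depends. The article does plan 95% confidence limits where appropriate, but does not tie the reading of a null result to them.

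**Conclusion.** The point holds in limited form. The calculation is right given SD 5. What is unsupported is the use of SD 5 for the ventilator-free-day score, and with it the unconditional statements that the trial is large enough. Over the assumed range of 5–35% zeros (mean 20 and SD 5 among the rest), t-test power for 1 day falls from the stated 80% to between 58% and 27% at 397 evaluable patients per arm, and the difference detectable with 80% power rises from about 1.0 to between 1.3 and 2.1 days. Even with no losses at all (476 per arm), power is 65% to 32%. The direction follows from the form of the endpoint; the size depends on inputs that the trial's own data can supply.

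**What to change.** 1. Estimate the pooled SD of ventilator-free days from patients already recruited, without arm labels. The article says that the trial is recruiting, so this can be done without unblinding and at no cost in alpha.
2. In Statistical considerations, state that SD, the power for a 1-day difference and the difference detectable with 80% power, with SD 5 kept alongside for comparison. Note that this is t-test power, while Statistical analysis plans Cox regression.
3. Qualify the power claims in the opening and closing paragraphs of the Discussion and in the Discussion part of the Abstract, so that each carries its condition.
4. Commit to interpreting a null result by the confidence interval for the difference, including whether that interval excludes 1 day.

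The cost is one blinded calculation and some rewording. The downside is that the stated power becomes less favourable. No extra patients are asked for, and the endpoint and the planned analysis stay as they are.

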### Randomization and blinding

Randomization will be performed using a dedicated, password protected, SSL-encrypted website with ALEA® software (TenALEA consortium, Amsterdam, The Netherlands) using random block sizes and is stratified only per ICU and per intubation location (that is intubated in the ICU or before ICU admittance in the emergency room or operation room). When, after randomization, consent is rejected, the patient is excluded. Due to the nature of the intervention, blinding is not possible.

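### Randomised patients are removed and replaced if consent is refused or not obtained within 24 h, so the primary set is randomised-and-consented and not the intention-to-treat set the article states

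*Protocol article*

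**What the plan says.** The Protocol article, under Statistical considerations, randomises first and asks the legal representative afterwards, with a limit of 24 h from randomisation. Removal has two triggers: refusal, and consent that has not been obtained by the limit. In either case "the patient is excluded and data will no longer be used, nor will this patient be counted for the sample size". A new patient is recruited instead, "until the total number of 476 patients in each arm is definitively included".

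Randomization and blinding describes removal only when consent is rejected. It also says that blinding is not possible and that allocation is made "using random block sizes and is stratified only per ICU and per intubation location".

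Statistical analysis then says: "Statistical analysis will be based on the intention-to-treat principle". No qualification follows. The Discussion relies on the same principle to keep patients in the trial who turn out to have ARDS.

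Study endpoints counts days to day 28 on which the patient is alive and has been off invasive ventilation for at least 24 consecutive hours. The article gives no separate rule for a patient who dies, or whose representative cannot be reached, before consent.

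**The concern.** Membership of the analysis set depends on something that happens after allocation, during up to 24 h of known treatment. Such a set is not the set of all randomised patients, so the intention-to-treat label does not describe it.

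The wider trigger matters most. A refusal is a decision by the representative that the trial must respect. Consent that was merely not obtained can also mean that the patient died first or that nobody could be reached. A patient who dies within 24 h of randomisation cannot have had 24 consecutive hours off the ventilator and scores 0. The rule can therefore remove patients from the bottom of the primary endpoint, and early deaths from the ICU, hospital and 90-day mortality endpoints. If the number removed differed by arm, the protection given by randomisation would be partly lost. The Discussion's safeguard of blinded analysis acts only after this selection has taken place.

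**Working it through.** **1. The plan's own size.** Inputs from Statistical considerations: "statistical power to detect a difference of 1 ventilator-free day and alive at day 28", "assuming that the common standard deviation is 5", a two-group *t*-"test with a 0.05 2-sided significance level", 80 % power.

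n per group = 2 × (1.96 + 0.8416)² × 5² / 1² = 2 × 7.849 × 25 = 392.4, so 393. The exact noncentral *t* calculation gives 394. The stated 397 has 80.4 % power, so it reproduces. 397 × 1.2 = 476.4, stated as 476, and 2 × 476 = 952. The 20 % is for dropouts and loss to follow-up. Patients removed for want of consent are replaced on top of it, so this point does not change the sample size.

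**2. The rules side by side.**

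- Randomization and blinding: removed if consent is rejected.
- Statistical considerations: removed if consent is refused or not obtained within 24 h.
- Statistical analysis: all patients as randomised.

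These define three different populations. Only the second states in detail what happens to the data and the count, so it is the one that would operate.

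**3. Sensitivity of the primary comparison.** Suppose there is no treatment effect and both arms have mean μ ventilator-free days over all randomised patients. Removing a share d of patients who score 0 raises that arm's mean to μ/(1 − d). If the arms lose shares d₁ and d₂, the false difference is μ/(1 − d₁) − μ/(1 − d₂), which is zero when d₁ = d₂. With d₂ = 0 it is μd/(1 − d). Both μ and d are assumptions, because the article gives neither.

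The last column is the two-sided error of a nominal 5 % comparison of means. It uses the plan's SD of 5 and 476 per arm, so the standard error is 5 × √(2/476) = 0.324.

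| d | μ = 15 | μ = 18 | μ = 20 | Two-sided error, μ = 15 to 20 |
|---|---|---|---|---|
| 1 % | 0.15 | 0.18 | 0.20 | 0.08 to 0.10 |
| 2 % | 0.31 | 0.37 | 0.41 | 0.16 to 0.24 |
| 5 % | 0.79 | 0.95 | 1.05 | 0.68 to 0.90 |

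For example, 18 × 0.02/0.98 = 0.37 day. With 476 retained, a 2 % loss is 476/0.98 − 476, about 10 patients.

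Three limits apply. The excess loss is taken to consist entirely of zeros. The shift is in means, whereas Statistical analysis names Cox regression for the primary outcome. The table shows sensitivity and does not estimate what happened in this trial.

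**4. The count per arm.** Five ICUs by two intubation locations give 10 strata. I simulated stratified permuted blocks with recruitment until both arms hold at least 476. Block sizes of 4, 6 and 8, the centre shares and the loss rates are assumptions.

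| Consent loss | Exactly 476/476 | Mean overshoot of larger arm |
|---|---|---|
| None | 22 % | 2 |
| 5 % | 10 % | 6 |
| 10 % | 9 % | 8 |
| 20 % | 5 % | 11 |
| 8 % v 12 % by arm | 1 % | 22 |

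At least 476 per arm was always reached. Exact equality was uncommon. Stopping on the total costs almost nothing: a split of 470/482, for example, gives 1/470 + 1/482 = 0.004202, the same to four figures as 2/476 = 0.004202.

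**The case against.** The strongest reply is that deletion without consent is an ethical and legal matter that statisticians cannot simply overrule. The review board approved the protocol, and whether it would let data be kept without consent cannot be judged from the article. The rule is also disclosed: the article separates provisional from definitive inclusion, and its Discussion applies intention-to-treat to patients already in the trial. The Discussion puts representative consent at up to half a day on average, inside the 24 h window, and the full protocol may hold a rule for deaths before consent.

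Much of this stands. It limits what can be asked for and rules out any claim that losses were large. It does not reconcile the two removal triggers, and disclosing a rule does not make the resulting set intention-to-treat.

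A reader might infer three stronger things, none of which the article supports:

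- **That the primary result is biased by a known amount.** There is no rate of consent loss, no rate of death within 24 h and no sign of a difference between arms. Patients whose consent is refused or whose representative is not reached are not shown to score 0. That relatives decide according to how the assigned ventilation is tolerated is conjecture.
- **That 476 per arm cannot be met.** At least 476 per arm can always be reached with a modest overshoot. Only exact equality is unlikely.
- **That late allocations would be forced or predictable.** No section closes a full arm or overrides the randomisation website.

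Reporting removals by arm and a bounding sensitivity analysis would be useful, but they are ordinary analysis-plan content and their absence here is no fault.

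**Conclusion.** The point holds as a mismatch between the stated analysis principle and the stated removal rule. The primary set is randomised-and-consented patients. The two sections that describe removal disagree on the trigger, and the wider one, read literally, discards deaths and unreachable representatives before consent.

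Bias is possible and has not been shown. Its size depends wholly on a differential loss that the article does not quantify. With an assumed mean of 15 to 20 days, a 2-point difference in removed zeros would move the difference in means by 0.31 to 0.41 day, roughly a third of the 1-day target. Equal losses would produce no false difference.

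The per-arm count is a minor wording matter: exact equality at 476 cannot be guaranteed and is not needed.

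**What to change.** 1. Align Randomization and blinding with Statistical considerations so that only actual refusals lead to deletion of data.
2. Ask the review board whether patients who die, or whose representative cannot be reached, before consent may be kept. As far as it agrees, analyse them in the arm to which they were randomised.
3. If the board declines, change Statistical analysis to name the primary set as randomised-and-consented (modified intention-to-treat).
4. Replace the per-arm quota by a stop at 952 consented patients in total.

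Items 1 and 2 need an amendment and an ethics question, which the board may answer in the negative. Items 3 and 4 are changes of wording. The sample size basis stays at 397 per group before inflation. The article reports the trial as still recruiting, so the question is best put now: data no longer kept may not be recoverable later.
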